## Abstract

**Background:**

Physical activity (PA) is beneficial for all people; however, people affected by multiple sclerosis (MS) find regular PA challenging. These people may include individuals with advanced disabilities and their care partners.

**Objective:**

The objective of this study is to determine the feasibility of a dyadic PA intervention for people with advanced MS and their care partners.

**Methods:**

This study is a randomized controlled feasibility trial of a 12-week intervention, with 1:1 allocation into an immediate intervention condition or delayed control condition. A target of 20 people with MS–care partner dyads will be included. The outcomes will be indicators of process, resources, management, and scientific feasibility. Participant satisfaction with the intervention components will be evaluated using a satisfaction survey. The subjective experience of participation in the study will be explored using semistructured interviews.

**Results:**

The project is funded by the Consortium of Multiple Sclerosis Centers. This protocol was approved by the Ottawa Hospital Research Ethics Board (20190329-01H) and the University of Ottawa Research Ethics Board (H-09-19-4886). The study protocol was registered with ClinicalTrials.gov in February 2020. The findings of this feasibility trial will be disseminated through presentations at community events to engage the MS population in the interpretation of our results and in the next steps. The results will also be published in peer-reviewed journals and presented to the scientific community at national and international MS conferences.

**Conclusions:**

The data collected from this feasibility trial will be used to refine the intervention and materials in preparation for a pilot randomized controlled trial.

**Trial Registration:**

ClinicalTrials.gov NCT04267185; https://clinicaltrials.gov/ct2/show/NCT04267185.

**International Registered Report Identifier (IRRID):**

PRR1-10.2196/18410

## Introduction

### Background

Multiple sclerosis (MS) is a neurodegenerative disease characterized by a variable course and largely unpredictable exacerbations leading to progressive disability [1]. Within 15-20 years of disease onset, it is estimated that approximately 50% of people with MS will require a walking aid (eg, cane) to walk about 100 m with or without rest (ie, Expanded Disability Status Scale [2] score≥6) [3]. Approximately 40%-80% of people with MS with walking impairment report a need for support from informal care partners to engage in everyday activities and to participate in aspects of daily life that are important and meaningful to them [4-6]. Care partners are relatives, family members, or friends who provide a broad spectrum of assistance, ranging from help in activities of daily living to emotional support for people with MS [7]. Although there are positive aspects of MS caregiving [8], the negative effect on care partners’ own well-being is often great. MS care partners report poorer quality of life than the general population [9]. These MS care partners also experience a higher level of activity limitations, more emergency department visits, and hospitalizations than care partners of people with other chronic diseases [10]. Together, this evidence suggests that MS has life-altering consequences for people with MS and their care partners and points to an opportunity to identify strategies to improve the health of *both* partners to the benefit of each individual and the dyad (ie, partnership).

Physical activity (PA) is a health-promoting behavior in the general population and an emerging strategy for managing MS [11]. Researchers have reported that PA interventions that incorporate behavioral strategies (eg, goal setting) can increase PA levels and improve symptomatic and participatory outcomes among people with mild-to-moderate MS [12,13]. Emerging evidence from other chronic disease contexts (eg, dementia) suggests that dyadic behavioral PA interventions (ie, targeting *both* care recipients and care partners) can increase PA levels, improve physical and psychological health, and improve exercise adherence for both individuals [14,15]. Other researchers have reported a reduction in stress and improvement in coping skills among care partners of people with dementia after dyadic PA interventions [16,17]. Despite the promise of dyadic PA interventions, no studies to date have capitalized on the potential benefits of including both people with advanced MS and their care partners together as *active participants* in a dyadic behavioral PA intervention. We contend that a dyadic behavioral PA intervention could improve the well-being of people with MS and could help care partners maintain their roles for longer periods with lower health risks.

Within the literature specific to people with MS, there is limited research on behavioral PA interventions that can be widely disseminated for people with advanced MS who experience mobility and transportation limitations [18] and require high levels of caregiving support [19]. Dyadic health researchers have also been challenged to integrate telerehabilitation into intervention design to provide more sustainable and widely disseminated behavioral interventions for dyads with chronic health conditions [20]. Telephone delivery is one of the most widely available telerehabilitation modalities and holds distinct promise for its potential for adoption by public health systems and organizations (eg, MS Societies) that routinely provide telephone support for people with chronic health conditions [21,22]. In particular, group-based teleconferencing offers the added benefit of social modeling, social support, and opportunities for vicarious learning experiences [23,24]. Collectively, existing evidence suggests that telephone-based PA interventions have the potential to increase PA and improve the health of people with MS and their care partners.

### Objectives

The objective of this study is to conduct the first randomized controlled trial (RCT) to determine the feasibility of a dyadic behavioral PA intervention—Physical Activity Together for People With Multiple Sclerosis (PAT-MS) and their care partners. Specifically, we will explore the 4 primary areas of focus of feasibility studies (ie, process, resources, management, and scientific feasibility) [25,26] recommended for PA studies involving people with MS [27].

## Methods

### Study Design

This protocol has been written following both the Standard Protocol Items: Recommendations for Interventional Trials and Consolidated Standards of Reporting Trials guidelines [28,29] (Multimedia Appendix 1). We will conduct a single site, assessor-blinded, parallel group, randomized controlled feasibility trial using a 1:1 allocation into an immediate intervention condition or a delayed intervention condition. A delayed intervention condition was deemed appropriate for PAT-MS based on the decision framework for appropriate control conditions for behavioral intervention trials [30,31].

### Participants

#### Sample Size

As a feasibility trial, this study will provide robust estimates of the likely rates of recruitment and retention as well as estimates of the variability of the proposed scientific outcomes to inform a well-designed pilot RCT. With these considerations in mind, our goal is to recruit 10 people with MS–care partner dyads per condition within a 6-month recruitment window, consistent with sample size guidelines for feasibility trials [32] and previously published exercise trials for people with advanced MS [33]. Enrolling 10 dyads per condition will account for approximately 15% attrition rate, as recommended for feasibility trials [34].

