#### Resource Outcomes

Resource outcomes will include assessing the rates of participant compliance (ie, number of practice activities, teleconference sessions, and one-on-one phone calls completed), attrition (ie, percentage of participants who drop out of the study and reasons for dropping out), suitability of eligibility criteria (ie, percentage of interested participants who meet the inclusion criteria and reasons for exclusion), and total cost of intervention delivery (ie, cost of equipment, personnel, and participant remuneration).

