### Data Management and Analysis

#### Quantitative Data Analysis

Data management and analysis will be performed using IBM SPSS Statistics for Windows (IBM Corp). Descriptive statistics, including means and SDs (continuous variables) and frequencies and proportions (categorical variables), will be used to summarize all demographic and feasibility data. Within-subject changes and effect sizes for improvement in scientific outcomes from T1 to T2 will be calculated using Cohen *d* separately for people with MS and care partners and by condition (immediate vs delayed control).

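### The sample size rests on a claim of robust recruitment and retention estimates, but at the planned attrition the 95% interval spans the plan's own 20% limit

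*Protocol article*

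**What the plan says.** The Sample Size section of the protocol article opens with what the trial is meant to yield: "this study will provide robust estimates of the likely rates of recruitment and retention". The same sentence then turns to the outcome measures: "as well as estimates of the variability of the proposed scientific outcomes to inform a well-designed pilot RCT". It then says that, with this in mind, "our goal is to recruit 10 people with MS–care partner dyads per condition within a 6-month recruitment window". Support for the number comes from published guidance and earlier exercise trials. No interval width or other precision target is given. On losses it says: "Enrolling 10 dyads per condition will account for approximately 15% attrition rate".

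The section on determining progression lists five criteria. Two matter here: at least half of the 20 dyads recruited within six months, and participant attrition below 20%. Resource Outcomes defines attrition per person, as the "percentage of participants who drop out of the study and reasons for dropping out".

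Under Quantitative Data Analysis, descriptive statistics (means and SDs, frequencies and proportions) "will be used to summarize all demographic and feasibility data". Within-subject changes and Cohen *d* are calculated separately by role and by condition.

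**The concern.** The plan claims a precision property and offers it as a reason for the sample size, so the claim can be tested against the plan's own numbers. If the interval around the expected attrition runs from clearly acceptable to clearly unacceptable, the estimate is not robust in any useful sense.

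The consequence falls on the attrition criterion. A result just below or just above 20% would be read as a pass or a fail, although the data could not tell a true rate well under the limit from one well over it. A reader who relied on the claim would give the retention and monthly recruitment figures more weight than they can bear.

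**Working it through.** **Inputs, all from the protocol article.** 10 dyads per condition, so 20 dyads or 40 people; a six-month window; about 15% attrition (Sample Size). Attrition limit below 20%; recruitment minimum 50% × 20 = 10 dyads (progression section). Attrition counted per person (Resource Outcomes).

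**The plan's own figure.** No formula or precision target is given, so 20 cannot be derived. The attrition allowance is coherent: 20 × 0.85 = 17 dyads expected to complete, and 17 / 0.85 = 20.

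**Retention.** The exact (Clopper-Pearson) 95% interval for x events in n runs from the 2.5% quantile of Beta(x, n − x + 1) to the 97.5% quantile of Beta(x + 1, n − x). The protocol does not say how far partners drop out together, so both extremes are shown.

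| Assumption | Attrition | 95% interval |
|---|---|---|
| Partners always leave together | 3/20 = 15% | 3.2% to 37.9% |
| All 40 people independent | 6/40 = 15% | 5.7% to 29.8% |

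The 20% limit is inside both intervals. The Wilson interval for 3/20, 5.2% to 36.0%, leads to the same reading.

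**How the attrition criterion behaves.** Below 20% means at most 3 of 20 dyads, since 4/20 = 20%. If people are counted as independent, it means at most 7 of 40, since 8/40 = 20%. The table gives the binomial probability that the criterion is met.

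| True attrition | P(X ≤ 3), n = 20 dyads | P(X ≤ 7), n = 40 people |
|---|---|---|
| 15% | 65% | 76% |
| 20% | 41% | 44% |
| 25% | 23% | 18% |

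At the rate the plan itself allows for, the criterion is missed about one time in three at dyad level and one time in four under independence.

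**Recruitment per month.** Take the count in a fixed six months as Poisson. The exact limits for 20 are χ²(0.025; 40 df)/2 = 12.2 and χ²(0.975; 42 df)/2 = 30.9. Divided by 6, this is 2.0 to 5.1 dyads per month around 20/6 = 3.3, about a 2.5-fold range.

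**Recruitment as a proportion.** Process Outcomes describes recruitment through response to the recruitment strategies, continued interest after screening, and refusals. The denominator would then be the people or dyads approached or screened, and its size is not stated. For assumed denominators the exact 95% intervals are: 20/40, 34% to 66%; 20/60, 22% to 47%; 20/100, 13% to 29%; 20/200, 6% to 15%.

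**Outcome variability.** The 95% limits for an SD, as multiples of the estimate, are √(df/χ²(0.975; df)) and √(df/χ²(0.025; df)). Pooling the two arms within one role gives 10 + 10 − 2 = 18 df: √(18/31.53) = 0.76 and √(18/8.23) = 1.48. With 17 completers (15 df) the limits are 0.74 and 1.55.

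**The case against.** Twenty dyads may be perfectly acceptable for a feasibility trial. No stated figure is wrong, and the number is tied to published guidance that is not at hand. That stands: the fault lies in the claimed precision, not in the sample size.

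Attrition is defined per participant, so the interval on 20 dyads is the wide end of the range. That also stands, and it is why both ends are shown. Even full independence, the most favourable of the two, leaves 20% inside the interval.

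Several stronger readings are tempting, and the document does not support them:

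- *The plan claims robust estimates of variability.* In the sentence, the adjective governs recruitment and retention only. Variability is called simply estimates.
- *No feasibility criterion can be judged.* For recruitment, the interval of 12 to 31 dyads around 20 excludes the 10-dyad minimum. The difficulty is shown for attrition. Compliance, satisfaction and serious adverse events were not examined.
- *The plan accepts 10 dyads as enough for robust estimates.* The 50% figure is one of five criteria for considering progression. It is not the planned size, and the precision claim is not attached to it.
- *The analysis will hide the imprecision.* The list of descriptive statistics is introduced as inclusive, frequencies are planned, and an article may leave intervals to a fuller document. Their absence here is not a fault in itself.
- *The next trial will be mis-sized from these SDs.* The plan says they will inform a pilot trial. It does not say that its sample size will be computed from them. Progression is also allowed where strategies to overcome challenges can be identified.

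**Conclusion.** The claim of robust recruitment and retention estimates is not borne out by the design. It fails most clearly for retention: at 15% attrition the upper 95% limit is between 30% and 38%, depending on how strongly partners' dropout is linked, against a limit of 20%. The monthly recruitment rate is uncertain by a factor of about 2.5. A recruitment proportion could be tighter or looser than that suggests, because its denominator is not stated.

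These results assume that observed attrition equals the planned 15%, that dropout is independent between dyads, and that recruitment is a Poisson count over the full six months. Small-group teleconferences could add some dependence between dyads; this was not modelled.

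The point limits what can be concluded about attrition. It does not undermine the trial or call for more participants.

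**What to change.** - In Sample Size, replace *robust* with *preliminary* and state the expected precision. For retention of 17/20 dyads that is a 95% interval of 62% to 97%; for recruitment of 20 dyads in six months it is 2.0 to 5.1 per month.
- Report the feasibility proportions used for progression with 95% intervals that allow for clustering within dyads.
- In the progression section, say that the attrition criterion will be read alongside its interval, not as a bare pass or fail.
- If outcome SDs are used to inform the pilot trial, report each with a 95% interval, pooled over arms within role.

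The cost is a few changes of wording and some intervals in the report. No participants, visits or design changes are added. The drawback is that the stated precision will look less favourable than it does now.

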#### Recruitment and Enrolment

Potential participants will be provided with a study information sheet at the local MS clinic and asked for consent to be contacted by the research team. A research coordinator will then contact interested participants by phone to discuss the study and conduct eligibility screening.

The inclusion criteria for people with MS are as follows: (1) a neurologist-confirmed MS diagnosis and stable course of disease-modifying therapies over the past 6 months, (2) an Expanded Disability Status Scale score between 6.0 and 6.5 based on a neurostatus-certified assessor examination, (3) relapse free in the past 30 days, and (4) having a care partner (ie, relative or close friend) who provides ≥1 hour per day of unpaid assistance or help. Additional inclusion criteria for both people with MS and care partners are as follows: (1) ≥18 years of age, (2) currently inactive (ie, purposeful exercise ≤2 days per week for 30 min), and (3) asymptomatic (ie, no major signs or symptoms of acute or uncontrolled cardiovascular, metabolic, or renal disease) based on the Get Active Questionnaire. The exclusion criteria for both people with MS and care partners are (1) presence of other neurological conditions and (2) inability to communicate in English.

### Study Procedures

Figure 1 presents the flow of participants throughout the study. All eligible participants will be scheduled for a baseline assessment (T1) for the provision of informed consent and collection of baseline data (scientific feasibility outcomes) at a university research laboratory. People with MS and their care partners will complete the measures in separate rooms to ensure privacy and confidentiality during the data collection process. Outcome measures will be collected by treatment-blinded assessors who are experienced with the administration of the proposed measures. In the 7 days following the baseline assessment, both people with MS and their care partners will be asked to wear an accelerometer during all waking hours. The accelerometer will be placed in a pouch on an elastic belt worn around the waist, with the device placed on the nondominant hip. Prestamped, preaddressed envelopes will be provided for the return of the accelerometer. Randomization will occur after baseline data collection.

The randomization sequence will be generated by an independent biostatistician using 1:1 permutated block randomization. Variable-sized blocks will be used to ensure approximately equal numbers in the 2 trial conditions. Participants will then complete the immediate intervention condition or the delayed intervention condition (ie, maintenance of usual activities) for 12 weeks. The same scientific feasibility outcomes as the baseline will be repeated immediately after the intervention (T2). We anticipate that each assessment session will last for approximately 2 hours. At the completion of the intervention, participants will also be asked to complete a satisfaction survey and an individual exit interview to assess their satisfaction with specific intervention components (ie, intervention content, interventionist, and delivery method) and their subjective experiences of participation in all aspects of PAT-MS, respectively. People with MS and their care partners will complete the same surveys. We anticipate that the survey will take approximately 15 minutes to complete. Individual exit interviews will be conducted over the phone by a member of the research team and will last for approximately 30 minutes. The same interview guide will be used for people with MS and their care partners. Participants in the delayed intervention condition will receive the intervention after the postintervention assessment (T2). We will follow the same intervention delivery procedures for the delayed condition as for the immediate intervention condition.

**Figure 1 figure1:**
[figure not shown]
Flow of participants through the study. CAREQOL-MS: Caregiver Quality of Life in Multiple Sclerosis Scale; CD-RISC-10: Connor-Davison Resilience Scale; DAS-7: Short-form Dyadic Adjustment Scale; GLTEQ: Godin Leisure-Time Exercise Questionnaire; ISEL-12: Interpersonal Support Evaluation List-12; MeEAP: Measure of Experiential Aspects of Participation; MS: multiple sclerosis; MSIS-29: Multiple Sclerosis Impact Scale-29; MSSE: Multiple Sclerosis Self-Efficacy Scale; PAT-MS: Physical Activity Together for People With Multiple Sclerosis.

### Intervention

PAT-MS is a dyadic behavioral PA intervention approach that incorporates a toolbox of evidence-based strategies adapted from previous trials on promoting PA in care partners of people with Alzheimer disease [35,36], a comprehensive program of research [20,37-39], and input from people with MS and care partners. PAT-MS is grounded in the theory of dyadic illness management [40]. Behavior change techniques [41] that target key theoretical constructs from the social cognitive theory [42] and self-determination theory [43] are included to facilitate behavior change. The social cognitive theory and self-determination theory have proven effective for increasing PA in the general population [44] and among people with MS [45-47]. Table 1 provides a summary of the content and main behavior change techniques [41] that will be targeted across the six teleconference sessions. In brief, the intervention includes the following main components:

Education: Participants will be provided with a PAT-MS manual that includes information on PA and introduces the concepts of shared appraisal of disease impact and dyadic coping. The benefits of shared participation in PA as a coping strategy to optimize well-being at the individual and dyadic levels will be discussed.Guidance from a trained interventionist: Participants will be provided with specific verbal and written guidance to improve their confidence in engaging in PA behavior. Given that PA interventions are more effective when combined with behavior change techniques [48], PAT-MS will include techniques commonly used in dyadic health interventions for persons with chronic neurological conditions and their care partners [20]. These techniques include, but are not limited to, goal setting and review, problem solving and action planning, behavioral practice, and instruction from a credible source.Social support: Participants will be provided practical, emotional, and informational social support during the intervention (eg, links to community programs for continued PA participation and opportunities to engage with and learn from other group members).

### Intervention Structure and Delivery

People with MS–care partner dyads will receive six group teleconferencing sessions (approximately 60 min each) every other week for a period of 12 weeks (Table 1). Each session is structured to include a review of material from the previous week, teaching content, group discussions, and explanation of practice activities to be completed before the next session. The group sessions will be interspersed with brief (approximately 15 min each) one-on-one support telephone calls in the weeks in which the group sessions do not occur. The intervention schedule will provide regular contact with the research team but will recognize the time commitment of the participants. We will seek to have 2-3 dyads on each teleconference call to manage the call more easily and to monitor the intervention process. The group-based teleconference format will provide opportunities for social modeling, social support, and vicarious learning experiences [23,24], which in turn will support behavior change, consistent with the theoretical foundations of PAT-MS [42,43]. Makeup sessions will be offered to those who miss teleconference sessions. The intervention will be delivered by a trained interventionist who will be provided with a structured manual for intervention delivery. Compliance to the protocol by the interventionist will be monitored using a checklist, weekly review meetings, and episodic monitoring of the teleconference sessions according to the guidelines of Bellg [49].

